## PEACOC

---

### 10.5. Assessments on Completion of Trial Treatment

After the end of initial and re-treatment periods, each patient will have an end of treatment visit which will be conducted after  $30 \pm 7$  days from last treatment administration / decision to discontinue, before entering the follow-up period. If previous imaging was obtained within 4 weeks prior to the date of discontinuation, then imaging at treatment discontinuation is not mandatory. In participants who discontinue study treatment due to documented disease progression, this is the final required trial tumour imaging.

All AEs that occur during this period should be recorded.

Patients who are eligible for re-treatment with pembrolizumab (as described in Section 9.3.3) may have up to two end of treatment follow-up visits, one after the initial treatment period and one after the re-treatment period.

Assessments to be completed at the end of treatment are:

- **Concomitant Medication review**
- **Adverse Events review**
- **Additional anti-cancer treatment review**
- **Survival status**
- **Full physical exam**
- **Vital signs and weight**
- **ECOG PS**
- **CT scan assessable by RECIST v1.1**
- **CT scan or MRI scan** assessable by RECIST v1.1) (abdomen, pelvis, and brain (if patient assessed with brain metastases at baseline), if the patient has not stopped treatment due to progression)
- **Full blood count**
- **Liver function tests, urea & electrolytes**
- **Thyroid function tests (Total T3/Free T4 and TSH)**
- **Serum calcium**
- **Urinalysis**
- **Urine or serum pregnancy test** (if applicable)
- **CA 125**
- **Biopsy** (if patient stopped due to confirmation of progressive disease) – should be performed within 6 weeks of patient discontinuing treatment\*.
- **Exploratory research bloods** (if patient stopped due to progression): PBMCs and plasma, please refer to the lab manual for details.
- **QoL: FACT-O**

\*In the event of any local covid-19 restrictions impacting resource at site to perform the biopsy as scheduled, the biopsy may be performed at a later timepoint, if it becomes possible and safe to do so later on, and as long as the patient has not proceeded with further cancer treatment Site must contact the CTC prior to this been re-arranged for approval from the CI/TMG.

## 10.6. Assessments During Follow Up (before progression)

Patients will have post-treatment follow-up for disease status, until disease progression, death, withdrawing consent, or becoming lost to follow-up.

These patients who discontinue trial treatment for a reason other than disease progression should be assessed **every 12 weeks** ( $84 \pm 7$  days), following the end of treatment, by radiologic imaging to monitor disease status. Every effort should be made to collect information regarding disease status until disease progression, death, end of the study or if the patient begins re-treatment with pembrolizumab as detailed in Section 9.3.3. Information regarding post-study anti-cancer treatment will be collected if new treatment is initiated.

Patients who are eligible and have consented to receive re-treatment with pembrolizumab according to the criteria in Section 9.3.3 will move from the follow-up phase to the re-treatment period when they experience disease progression.

Assessments to be completed during follow-up are:

- **Adverse Events review** as per requirements detailed in the pharmacovigilance sections 13.2.1 (AE), 13.2.2 (SAE) and 13.4 (AESI)
- **CT scan of chest, assessable by RECIST v1.1**
- **CT scan or MRI scan** assessable by RECIST v1.1) (abdomen, pelvis, and brain (if patient assessed with brain metastases at baseline)
- **Additional anti-cancer treatment review**
- **Survival status**
- **QoL: FACT-O**
- **Biopsy** (if first disease progression on the trial during the follow-up period has been confirmed) – should be performed within 6 weeks\*.

\*In the event of any local covid-19 restrictions impacting resource at site to perform the biopsy as scheduled, the biopsy may be performed at a later timepoint, if it becomes possible and safe to do so later on, and as long as the patient has not proceeded with further cancer treatment Site must contact the CTC prior to this been re-arranged for approval from the CI/TMG.

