## 4. TRIAL DESIGN

- This is a multi-centre, single arm, phase II trial in patients with advanced clear cell gynaecological cancer who have received at least one line of chemotherapy.
- Patients will receive pembrolizumab 200 mg intravenously every 3 weeks (Q3W) with a re-treatment option for those who respond as described below\*.
- Using a single stage A'Hern design, 48 patients will be enrolled.
- Patients will have a fresh tumour biopsy at baseline, 6-8 weeks after start of treatment and on disease progression (if consent obtained).
- Archival tumour will also be obtained

The primary objective of this study is to determine the PFS rate at 12 weeks with pembrolizumab in patients with advanced clear cell gynaecological malignancies who have received at least one prior line of chemotherapy. The trial will be considered positive (i.e. the null hypothesis will be rejected) if 12 or more patients are progression-free (i.e. have partial or complete response or are stable) at 12 weeks.

All imaging obtained on study will be assessed using RECIST v1.1 for determination of PFS and ORR endpoints.

Adverse events will be monitored throughout the trial and graded in severity according to the guidelines outlined in the NCI CTCAE version 5.

The initial phase of trial treatment with pembrolizumab will continue until any of the following have occurred:

- two years of initial phase of study treatment has been administered
- documented and confirmed disease progression by RECIST v1.1 criteria
- unacceptable adverse event(s)
- intercurrent illness that prevents further administration of treatment
- investigator's decision to withdraw the patient
- patient withdraws consent
- pregnancy of the patient
- non-compliance with trial treatment or procedure requirements

\*In patients who attain a confirmed complete response (CR) (i.e. a second scan confirming the presence of a CR according to RECIST criteria v1.1) during the study, the treating clinician may consider stopping trial treatment. These patients will be eligible for re-treatment with pembrolizumab for up to one year after they have experienced radiographic disease progression at the discretion of the investigator as well as in accordance with the criteria in section 9.3.2. This re-treatment will be considered the Second Course Period (Re-treatment) .

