## **18. STATISTICS**

### **18.1. Sample Size Calculation**

Assuming that the proportion of progression-free patients at 12 weeks will be 33%, a proportion <15% would be of no further interest [16]. Using A'hern's single-stage phase II design with 90% power and one-sided 5% significance level, a sample size of 48 patients is required with  $\geq 12$  patients alive and progression-free at 12 weeks to warrant further investigation. The sample size was calculated using "Sample size tables for clinical studies" software.

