### **18.2. Statistical analysis**

#### **18.2.1. Analysis of main endpoint**

The number and percentage of progression-free patients at 12 weeks will be presented, with 90% two-sided confidence intervals for the percentage.

The proportion of progression-free patients is defined as the number of patients alive with complete or partial response or stable disease maintained at 12 weeks (as assessed by the site radiologist and/or investigator, using RECIST v1.1) divided by the number of patients in the analysis population. Only patients with tumour assessment at or beyond 12 weeks will be considered progression-free.

All eligible patients who received at least one cycle of pembrolizumab will be included in the analysis population (i.e. safety population).

Any patient found to be ineligible will be excluded and replaced.

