### **18.2.2.4. Objective response at 12 weeks and best objective response**

Objective response is defined as a complete or partial response as determined by RECIST v1.1. Patients without a tumour assessment at 12 weeks will be considered to be non-responders. The proportion of patients with objective response at 12 weeks will be presented as a proportion with 90% two-sided confidence interval.

The best objective response consists of the best among all objective responses assessed. Best objective response will be reported as a proportion with 90% two-sided confidence interval. The analysis of best objective response will be performed with all patients over the whole study period (including Re-treatment phase). A subset analysis will be performed for patients in the Re-treatment phase, once over the whole study period and once over the Re-treatment phase only.

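### Most patients who stop treatment before week 12 without progression have no scheduled week-12 scan, because follow-up imaging is counted from the stop and not from first dose

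*Protocol*

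**What the plan says.** **On treatment.** Protocol sections 10.2 and 10.3.1 place tumour imaging at weeks 6 and 12 and then every 12 weeks, expressed as time on treatment. Section 10.2 keeps these time points, where feasible, if treatment is delayed. Section 10.4.2.2 keeps the pre-cycle assessments at study visits where no drug is given. Neither mentions discontinuation. Footnote L of Appendix 1 runs the 12-weekly imaging up to end of treatment.

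**At discontinuation.** Section 10.5 sets an end-of-treatment visit 30 ± 7 days after the last administration or the decision to stop, with imaging unless the patient stopped for progression. It adds: "If previous imaging was obtained within 4 weeks prior to the date of discontinuation, then imaging at treatment discontinuation is not mandatory".

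**After discontinuation.** For patients who stop for a reason other than progression, section 10.6 sets assessments every 84 ± 7 days, "following the end of treatment, by radiologic imaging to monitor disease status". Appendix 1 sets the same interval from discontinuation. Under section 10.6.1, a patient who starts a new anti-cancer therapy moves to telephone survival follow-up.

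**Scoring.** For the primary endpoint, section 18.2.1 says: "Only patients with tumour assessment at or beyond 12 weeks will be considered progression-free". For response at 12 weeks, section 18.2.2.4 says: "Patients without a tumour assessment at 12 weeks will be considered to be non-responders".

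**The concern.** The primary endpoint and one secondary endpoint are read at a fixed time, week 12 from start of treatment. Once a patient stops without progression, the imaging clock restarts from a different origin, and no passage retains the week-12 scan. The patients concerned are not a random subset: they are largely those who stop for toxicity. Section 9.5, Table 4 makes such stops foreseeable, since several immune-related events lead to permanent discontinuation and not to a delay. At stake are the week-12 response rate, which assigns non-response when there is no scan at 12 weeks, and to a lesser degree the count of progression-free patients on which the trial's decision rests.

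**Working it through.** **1. The plan's own design.** Section 18.1: "Assuming that the proportion of progression-free patients at 12 weeks will be 33%, a proportion <15% would be of no further interest"; "Using A'hern's single-stage phase II design with 90% power and one-sided 5% significance level", "a sample size of 48 patients is required". Section 4 calls the trial positive "if 12 or more patients are progression-free" at 12 weeks. With X binomial:

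- Type I error: P(X ≥ 12 | n = 48, p = 0.15) = 0.0478.
- Power: P(X ≥ 12 | n = 48, p = 0.33) = 0.9114.
- The smallest n with exact type I error ≤ 0.05 and power ≥ 0.90 is 48, with cut-off 12. The design reproduces.

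**2. When the scans fall.** Assume doses on schedule, so that dose k is given on day d = 21(k − 1), and take discontinuation as the date of last dose. Week 12 is day 84.

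- End-of-treatment scan: d + 30 ± 7, that is d + 23 to d + 37.
- First follow-up scan counted from last dose: d + 84 ± 7, that is d + 77 to d + 91.
- First follow-up scan counted from the end-of-treatment visit: d + 23 + 77 to d + 37 + 91, that is d + 100 to d + 128.

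| Last dose | Day d | End-of-treatment scan (week) | First follow-up scan, from last dose (week) | First follow-up scan, from end-of-treatment visit (week) |
|---|---|---|---|---|
| 1 | 0 | 3.3-5.3 | 11-13 | 14.3-18.3 |
| 2 | 21 | 6.3-8.3 | 14-16 | 17.3-21.3 |
| 3 | 42 | 9.3-11.3 | 17-19 | 20.3-24.3 |
| 4 | 63 | 12.3-14.3 | 20-22 | 23.3-27.3 |

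After doses 2 and 3 the end-of-treatment scan precedes week 12 and the first follow-up scan comes after it on either anchor. Two rows can yield a usable scan: dose 1 if the clock runs from last dose (weeks 11-13), and dose 4 if the end-of-treatment scan is done (weeks 12.3-14.3).

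The waiver matters here. With the week-6 scan on day 42, a discontinuation up to about day 42 + 28 = 70 leaves the end-of-treatment scan optional. That includes a stop soon after dose 4 on day 63.

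**3. How an early stopper is scored.**

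- Response at 12 weeks: with no scan at 12 weeks, a patient already in response is a non-responder (18.2.2.4).
- Primary endpoint, first later scan without progression: progression-free at week 12, correctly (18.2.1).
- Primary endpoint, first later scan with progression: whether progression came before or after week 12 is unknown, and 18.2.1 does not say how to score it.
- Primary endpoint, death or new therapy before that scan: no qualifying assessment, so not counted as progression-free.

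**4. Illustration of size.** The protocol gives no number of early stops without progression, so m = 1 to 5 is assumed. If m of the 48 patients are fixed as failures, success requires at least 12 among the remaining 48 − m:

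| m | Power, P(X ≥ 12 given 48 − m, 0.33) | Type I error, P(X ≥ 12 given 48 − m, 0.15) |
|---|---|---|
| 0 | 0.911 | 0.0478 |
| 1 | 0.895 | 0.0413 |
| 2 | 0.877 | 0.0354 |
| 3 | 0.857 | 0.0302 |
| 4 | 0.833 | 0.0255 |
| 5 | 0.807 | 0.0214 |

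**The case against.** A reader might infer that the primary endpoint cannot be scored correctly for patients who stop early. The documents do not support that. Section 18.2.1 accepts an assessment at or after 12 weeks, so a clean scan at week 14 or week 24 establishes week-12 status. Nor does the protocol say that a patient whose first later scan shows progression is a failure. Section 18.2.1 is silent, and the rule may sit in the analysis plan, which is not at hand.

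A reader might also infer a large loss of power. If 5%, 10% or 15% of would-be successes were lost, power would be 86.6%, 80.7% or 73.1%. Those rates are assumptions and allow no rescue by a later clean scan. If early stoppers share the 33% rate, a 15% loss means about 0.15 × 48 = 7 patients stopping early without progression, with none rescued. The protocol gives no basis for that figure.

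Further points narrow the gap:

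- Many toxicities in Table 4 lead to withholding, and those patients keep the calendar under 10.2 and 10.4.2.2.
- A late decision to stop can produce a usable scan. With last dose on day 42 and a decision after day 70, the waiver lapses and the visit falls no earlier than day 70 + 23 = 93.
- The waiver makes the scan optional; it does not forbid it.
- Section 10.3.1 and Appendix 1 footnote j continue imaging until progression.
- Scoring as failure is conservative, and best response and duration of response still capture early responders.
- The different PFS scan grid is minor in a single-arm trial that is 12-weekly after week 12 anyway.

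All of this limits the size. None of it schedules a scan at week 12 after a permanent stop, and an analysis plan cannot recover a scan that was never taken.

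**Conclusion.** The concern holds in a limited form. As written, most patients who stop before week 12 without progression have no scheduled week-12 scan; the exceptions are certain stops after dose 1 or dose 4 and late decisions to stop. For response at 12 weeks the consequence follows directly from the protocol's own rule. For the primary endpoint it is confined to patients whose first later scan shows progression and those who die or start new therapy before that scan.

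The number affected is unknown. On the assumption that 1 to 5 of 48 are fixed as failures, power falls from 91.1% to between 89.5% and 80.7%, and type I error falls from 4.8% to between 4.1% and 2.1%. One such patient is enough to take power just below the stated 90%, but scoring as failure does not favour a false positive. This is an inexpensive improvement worth making, not an error that invalidates the design: 48 patients and a cut-off of 12 stand.

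**What to change.** In sections 10.5 and 10.6 and Appendix 1:

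- Keep tumour imaging on the first-dose calendar (week 6, week 12, then every 12 weeks, ± 7 days) until RECIST progression or new anti-cancer therapy, whether or not treatment continues.
- State that the end-of-treatment imaging waiver does not remove the week-12 scan.
- Reconcile the anchors, which are end of treatment in 10.6 and discontinuation in Appendix 1.

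Patients who start new therapy before week 12 would still lack a qualifying scan, and the existing rule for them is unaffected.

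The cost is protocol wording and the Appendix 1 footnotes. A few patients would have a scan re-timed or one additional routine scan. Sample size and decision rule do not change.

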### 10.6.1. Survival Follow-up

Once a patient experiences confirmed disease progression or starts a new anti-cancer therapy, the patient moves into the survival follow-up phase and should be contacted by telephone every 12 weeks to assess for survival status and any AEs that require reporting as per section 13.2, until death, withdrawal of consent, or the end of the study, whichever occurs first.

## 11. EXPLORATORY BIOLOGICAL STUDIES

### 11.1. Tumour Tissue Collection and Exploratory Research Blood Sampling

One of the exploratory aspects of this study is to evaluate potential tumour and peripheral blood biomarkers including exome and RNA sequencing, with the objective of identifying biomarkers that predict response to pembrolizumab in patients with advanced clear cell gynaecological cancers. Patient consent to blood and tumour sample collection is included in the main trial consent form.

Detailed information on sample handling, storage and shipping are included in the Laboratory Manual.

#### 11.1.1. Biomarker Sample Collection

For each patient, the following samples will be collected (for both the initial and re-treatment periods) - please see the laboratory manual for specific guidance:

- Whole blood EDTA at baseline
- Circulating PBMCs at baseline, with cycles 2, 4, 6 then at 12 months and at the time of disease progression
- Circulating plasma at baseline, with cycles 2, 4, 6 then at 12 months and at the time of disease progression
- Archival tissue that was used to confirm diagnosis (from initial treatment)
- Fresh tumour tissue biopsy samples at baseline, 6-8 weeks during treatment and at the time of disease progression.

#### 11.1.2. Tumour Biopsies

At baseline, the fresh tumour biopsy will be obtained prior to administration of the first dose of pembrolizumab for all patients. The next fresh tumour biopsy will be obtained between Day 42 and 56 ( $\pm 7$  days) from first day of initial treatment and re-treatment if applicable and within 8 weeks of diagnosis of progressive disease (initial and re-treatment phases).

**N.B.** The requirement for sites to request a biopsy from the patient is mandatory at baseline, 6-8 weeks and upon progression during the initial treatment period, but optional during the re-treatment period.

The reason biopsies are taken for the trial must be clearly and fully explained to the patient before they enter the trial, and consent re-checked with the patient at the relevant time prior to the biopsy to be taken.

If a patient refuses mandatory biopsy collection whilst on trial, the CTC should be contacted immediately for CI & TMG review.

Any measurable lesion should be **SEPARATE** from the biopsied lesion. The biopsied lesion should **NOT** be used for measuring response. If the original biopsiable lesion is no

longer present or no longer suitable for biopsy at 6 weeks then another site should be chosen. If no other biopsiable site then a 6 week biopsy is not possible and this should be documented.

Additional non-trial biopsies may also be performed if clinically indicated (eg, for mixed responses).

For patients requiring serial image-guided core needle tumour biopsy, those biopsies will be performed according to institutional practice.

If clinically practical, at each fresh biopsy collection time point, patients should undergo 4 core biopsies as per local hospital procedures. The first and third core biopsies will be placed in formalin and processed for formalin-fixed, paraffin-embedded blocks, while the second and fourth core biopsies will be immediately frozen in liquid nitrogen or equivalent method and then stored at between -70°C to -80°C. In exceptional cases, excisional or punch biopsies are permitted and may be substituted if sufficiently large (4 mm or greater in diameter).

Please also refer to the PEACOCC laboratory manual for further details.

## 12. DATA MANAGEMENT AND DATA HANDLING GUIDELINES

Data will be collected from sites on electronic case report forms (eCRFs) designed for the trial and supplied by UCL CTC. SAEs & AESIs will be reported on paper reports. Data must be accurately entered / transcribed onto trial forms / reports and must be verifiable from source data at site. Examples of source documents are hospital records which include patient's notes, laboratory and other clinical reports etc.

Where copies of supporting source documentation (e.g. autopsy reports, pathology reports, CT scan images etc.) are being submitted to UCL CTC, the patient's trial number must be clearly indicated on all material and any patient identifiers removed/blacked out prior to sending to maintain confidentiality.

### 12.1. Completing Electronic Case Report Forms (eCRFs)

All eCRFs must be entered by staff who are listed on the site staff delegation log and authorised by the PI to perform this duty. The PI is responsible for the accuracy of all data reported in the eCRF and paper SAE/AESI reports.

All entries must be clear, legible and written in ball point pen. Any corrections made to a paper SAE/AESI report at site must be made by drawing a single line through the incorrect item ensuring that the previous entry is not obscured. Each correction must be dated and initialed. Correction fluid must not be used.

The use of abbreviations and acronyms should be avoided.

Originals of the paper SAE/AESI reports must be sent to UCL and a copy kept at site.

### 12.2. Missing Data

To avoid the need for unnecessary data queries, eCRFs must be checked at site to ensure there are no blank mandatory fields that require completion (unless it is specifically stated that a field may be left blank). For paper SAE/AESI reports, when data are unavailable because a measure has not been taken or test not performed, enter "ND" for not done. If an item was not required at the particular time the form relates to, enter "NA" for not applicable. When data are unknown enter the value "NK" (only use if every effort has been made to obtain the data). For eCRF data entry guidance, please refer to the PEACOCC eCRF manual for sites which can be found in the ISF.

### 12.3. Timelines for Data Completion

Electronic CRFs must be completed at site as soon as possible after the relevant visit and within one month of the patient being seen.

Sites that persistently do not complete data items within the required timelines may be suspended from recruiting further patients into the trial by UCL CTC and subject to a 'Triggered' monitoring visit. See section 15.3 (Triggered' On-Site/Remote **Monitoring**)

for details. Please refer to section 13, for the reporting timeframes required for SAEs/AESI and AEs.

